### Secondary objectives

To test whether any difference in the change in patient activation between the two groups still exists after controlling for potential covariates.To test whether the use of OWise leads to a smaller decrease in health status at 3-month follow-up than standard care after controlling for potential covariates.To test whether the use of OWise leads to a smaller decrease in HRQoL at 3-month follow-up than standard care alone after controlling for potential covariates.To test whether the use of OWise leads to a lower increase in psychological distress at 3-month follow-up compared to standard care alone after controlling for potential covariates.To test whether the use of OWise reduces the rate of resource utilization in the first year following diagnosis compared to standard care among patients registered in Discover, an integrated health and social care record in North West London.To test whether the use of OWise reduces the average cost per patient in the first year following diagnosis compared to standard care among patients registered in Discover.To describe the change in patient activation in the intervention group compared to the control group in the first year following diagnosis.To describe the level of OWise uptake in the intervention group in the first year following diagnosis.To describe the change in the pattern of patient activation, HRQoL, psychological distress, and health status in the intervention group compared to the control group in the first year following diagnosis.

### Procedure

#### Recruitment

We will continuously sample all patients meeting eligibility criteria diagnosed within the recruitment period. A member of the clinical team will identify eligible patients in multi-disciplinary team meetings or clinic lists and invite potential participants at diagnosis. The name of the digital tool will not be disclosed when inviting patients. If a patient shows interest, a researcher will provide further information either in person or over the phone. Patients can decide to take part any time before starting anti-cancer treatment.

After meeting eligibility criteria and providing written informed consent, participants will be randomized. The researcher will inform the participant of their allocation and provide instructions for accessing the online PROM collection tool. Participants in the intervention arm will be required to complete the baseline measure before using OWise.

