### Study design

We will evaluate the effectiveness of OWise using a multi-center, individually randomized, parallel controlled trial recruiting 122 patients. The intervention group will receive OWise plus standard care, while the control group will receive standard care alone to assess superiority. Due to the nature of the digital tool, it is not possible to blind participants or providers. Outcomes are reported directly by participants and analysis depends on the randomly assigned group. Therefore, outcome assessors and data analysts are not blinded either. Patients in both groups will complete patient-reported outcome measures (PROMs) to assess outcomes at baseline, 3, 6, and 12 months from diagnosis. See Fig. 2 for the SPIRIT diagram showing the schedule of enrolment and assessment and Additional file 1 for the SPIRIT checklist.

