### Participants

Females (aged 18 years or over) newly diagnosed with early stage breast cancer as a first primary diagnosis will be eligible to take part. Eligibility was restricted to early stage and first primary diagnoses as metastatic patients may have confounding care and psychosocial experiences and patient activation naturally increases with time after a breast cancer diagnosis [22]. Patients must complete the baseline measure before starting anti-cancer treatment. All participating sites are located in the UK, a list of which can be found on the registration website. Exclusion criteria include private care, difficulty reading in English, significant cognitive impairments or poor mental health, and no Internet access.

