### Sample size

Sample size calculations are based on the change in PAM-13 score from baseline to 3 months. A difference of four points is considered clinically relevant [29, 45]. In a similar study, the mean PAM-13 score at baseline for the intervention group was 61.3 (SD 16.61) and 67.9 (SD 16.85) at 3 months [46]. For the control group, the study reported a mean PAM-13 score at baseline of 62.1 (SD 17.30) and 62.8 (SD 14.94) at 3 months. Based on these findings, this study is planned to detect a mean change difference of 5.90 assuming a common standard deviation of 10.0. Using an 80% power, the study will recruit 47 patients per group. This was calculated using a two-sided test with alpha = 0.05. We will increase the sample size taking 23% attrition at 3 months into account (47/(1–0.23)) to 61 patients per group [47] and, as mentioned above, increase the sample size accordingly if contamination is found near the end of recruitment.

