#### Primary endpoint

We will compare the PAM-13 score change between the intervention arm and the control arm using independent *t* test. Data will be log-transformed to achieve normality as appropriate. We will also compare the mean change in PAM-13 score in the intervention and control arm in a multiple linear regression model including potential covariates.

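### Baseline PAM-13 is completed after participants are randomized and told their arm, so knowledge of allocation can bias the baseline half of the primary change score, in a direction the protocol cannot predict

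*Protocol article*

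**What the plan says.** The Recruitment section sets out the steps in order. First: "After meeting eligibility criteria and providing written informed consent, participants will be randomized". Next: "The researcher will inform the participant of their allocation and provide instructions for accessing the online PROM collection tool". Then a rule for one arm: "Participants in the intervention arm will be required to complete the baseline measure before using OWise".

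One other limit on baseline timing appears, for both arms, in the Participants section (the Abstract says the same): "Patients must complete the baseline measure before starting anti-cancer treatment". Nothing in the article requires baseline before randomization or before disclosure.

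On blinding, Study design says that "it is not possible to blind participants or providers" and that "Outcomes are reported directly by participants and analysis depends on the randomly assigned group".

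The primary analysis uses the baseline directly: "We will compare the PAM-13 score change between the intervention arm and the control arm using independent" *t* test. The trial is sized on the same quantity: "Sample size calculations are based on the change in PAM-13 score from baseline to 3 months". Under Secondary endpoints, the EQ-5D-5L, EORTC and HADS scale scores are also compared as changes.

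**The concern.** PAM-13 asks patients to rate their own knowledge, skills and confidence in managing their care. Learning that one has been given a self-management tool, or has not, could plausibly alter those answers before the tool has done anything. Baseline is meant to be the part of a change score that allocation cannot touch; under the stated order it loses that protection. The rule that baseline precedes use of OWise keeps out exposure to the tool, but not knowledge of the arm.

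Two things are at stake. The first is the validity of the primary comparison, since a distorted baseline could produce a false difference or hide a real one. The second is completeness. A woman who learns her arm and then does not complete baseline has already been randomized but has no observed change score, and such losses could differ by arm.

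**Working it through.** **1. Is the order stated or inferred?** Recruitment lists consent, then randomization, then disclosure together with access instructions for the questionnaire system. The rule that the intervention arm completes baseline before using OWise is needed only if baseline follows allocation. The two statements agree.

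**2. Reproduce the plan's own figure.** Inputs from Sample size: difference 5.90, SD 10.0, two-sided alpha 0.05, power 80%, 23% attrition.
- The cited study's means give (67.9 − 61.3) − (62.8 − 62.1) = 6.6 − 0.7 = 5.9.
- A two-sample *t* test at standardized difference 0.59 needs 46.08 per arm, rounded up to 47. Power at 47 per arm is 80.8%.
- Attrition: 47/0.77 = 61.04, stated as 61 per arm, 122 in total.

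The sample size stands on its own inputs, and the concern does not depend on it.

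**3. How a reporting shift enters the estimate.** Let b be the OWise-minus-control difference in PAM-13 reporting at baseline caused by knowing the arm, and u the same difference at 3 months. Then

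bias in the difference in change = u − b.

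If the baseline shift has gone by 3 months (u = 0), the bias is −b, the full size of the shift with its sign reversed. If it persists unchanged (u = b), it cancels.

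**4. Size, for u = 0.** The article gives no value for b, so 1, 2 and 3 points are assumed. They compare with the 4-point difference that the article calls clinically relevant. SE = 10 × √(2/47) = 2.06; two-sided 5% *t* test with 92 df, critical value 1.986; rejection probabilities from the noncentral *t*.

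| Size of shift (points) | Shift/SE | Two-sided type I error, no true effect | Difference left if shift runs against OWise, true 5.9 | Power |
|---|---|---|---|---|
| 0 | 0 | 5.0% | 5.9 | 80.8% |
| 1 | 0.48 | 7.7% | 4.9 | 65.2% |
| 2 | 0.97 | 16.0% | 3.9 | 46.5% |
| 3 | 1.45 | 30.2% | 2.9 | 28.5% |

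The type I column counts rejections in either direction, and nearly all of them fall on the side the bias favours. If baseline is raised in the OWise arm, the bias favours control, and the chance of wrongly declaring OWise superior falls from 2.5% to 0.7%, 0.2% or 0.03%. If baseline is lowered in the OWise arm, or raised among controls, the false claims favour OWise.

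**5. Would baseline adjustment repair it?** No. Pooling the cited study's SDs gives 16.96 at baseline and 15.92 at 3 months. With an SD of change of 10, the implied correlation is (16.96² + 15.92² − 10²)/(2 × 16.96 × 15.92) = 0.82, and the slope is 0.82 × 15.92/16.96 = 0.77. Adjustment would still carry about three quarters of the baseline shift into the estimate.

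**The case against.** Several points on the other side have force.

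- **Persistent shifts cancel.** Patients are unblinded at 3 months too. Point-for-point bias requires a baseline shift that has faded by then. One that persists drops out of the change score under the present order, and would remain in the 3-month score if baseline were moved ahead of disclosure. This stands: the reorder protects the baseline and does not cure unblinded reporting at follow-up.
- **Size and direction are unknown.** This stands. A reader might infer that the order favours OWise; the article does not support that. If having the tool raises reported confidence, the bias runs against OWise.
- **OWise instruction before baseline.** A reader might infer that intervention patients are shown how to navigate OWise before answering. The Intervention group section says the person enrolling the patient gives that instruction, but not when relative to baseline. Recruitment pairs disclosure with instructions for the questionnaire system, not for OWise.
- **Uneven completion.** A reader might infer that only the OWise arm has reason to complete baseline. Both arms are bound to complete it before anti-cancer treatment; only the additional rule about OWise use is arm-specific. No completion rates are given, so loss that differs by arm is possible but not shown.
- **Baseline as an entry condition.** The Participants section can be read as making a completed baseline part of eligibility, which would put it before randomization, or only as a timing rule. The schedule figure (Fig. 2), which might settle this, is not in the text available. The rule about OWise use favours the order described here, but the two sections need reconciling.

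**Conclusion.** The concern holds in a limited form. As written, baseline PAM-13 and the other questionnaire baselines are completed by patients who know their arm, and the primary *t* test uses that baseline directly. This creates a risk of bias; it does not show that bias will occur. The figures rest on 47 evaluable patients per arm, an SD of change of 10, and an assumed shift of 1 to 3 points that is absent by 3 months. On those assumptions the harm is as much lost power as a false positive. Post-randomization loss of baselines is a second, unquantified risk. The sample size and the choice of primary test are not in error on this account. The case for acting is that an uninformed baseline cannot be recovered by analysis once patients have been enrolled in this order.

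**What to change.** Amend Recruitment so that the order is: written consent; baseline questionnaires submitted in PROFILES; the randomization phone call; then disclosure of allocation and, for the intervention arm, OWise instructions. Reconcile the Participants section with this by making a submitted baseline, dated before the start of anti-cancer treatment, a precondition for the randomization call. Align the schedule figure if it shows another order.

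The cost is a wording amendment and a change to the site checklist. Randomization is already by phone, and the sample size stays at 61 per arm. Trial status gives recruitment as pending, so the change could be made before any patient is affected. The downsides are a short delay between consent and allocation, and that consenting patients who do not complete baseline are not randomized; under the present order they would be randomized and lack a baseline. The amendment should not be presented as removing unblinded reporting bias at 3 months, which would remain a limitation to acknowledge.

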### Measures

#### Primary outcome measure

##### Patient Activation Measure (PAM-13)

Patient activation describes the knowledge, skills, and confidence a person has in managing their health and care [23, 24]. The PAM-13 is a 13-item questionnaire that measures patient activation [25]. Each item has four response options from (1) ‘strongly disagree’ to (4) ‘strongly agree,’ and ‘not applicable.’ PAM-13 scores will be calculated according to the guidelines [25]. Scores range on a scale of 1–100 corresponding to four activation levels: 1 (≤ 47.0) not believing activation important, 2 (47.1–55.1) a lack of knowledge and confidence to take action, 3 (55.2–67.0) beginning to take action, and 4 (≥67.1) taking action [25]. This measure has been used widely among cancer patients and across the UK [26–28] and has robust evidence of reliability and validity [23, 29, 30]. Patient activation, as measured by the PAM-13, can be targeted by interventions and change over time [24]. Previous work has shown that higher patient activation is associated with better HRQoL and lower health care utilization [16–18, 31].

#### Secondary outcome measures

##### The European Organisation for Research and Treatment of Cancer Core Quality of Life Questionnaire (EORTC QLQ-C30 version 3) and Updated Breast Cancer Module (EORTC QLQ-BR45)

The EORTC QLQ C-30 is a 30-item instrument measuring HRQoL with five functional scales (physical, role, cognitive, emotional, and social), a global quality of life scale, eight symptom scales or items (fatigue, pain, nausea and vomiting, dyspnea, loss of appetite, sleep disturbance, constipation and diarrhea) and a single item assessing perceived financial impact [32]. The EORTC QLQ-BR45 contains five functional scales or items (body image, future perspective, sexual functioning, sexual enjoyment, and breast satisfaction) and seven symptom scales or items (systemic therapy side effects, upset by hair loss, arm symptoms, breast symptoms, endocrine therapy symptoms, skin mucosis symptoms, and endocrine sexual symptoms) [33]. Scores will be calculated according to EORTC guidelines [34]. All scores range from 0 to 100. Higher scores on functional scales and global quality of life indicate better function and HRQoL, respectively. Higher scores on symptom scales and items indicate higher symptom burden [35]. The measures have strong evidence of validity and reliability in early stage breast cancer patients and have been used in a number of clinical trials allowing for comparisons [33, 36].

##### Hospital Anxiety and Depression Scale (HADS)

This 14-item questionnaire measures psychological distress with seven items assessing anxiety, seven items assessing depression and the summed total score reflecting the level of psychological distress [37]. Three continuous scales will be calculated (anxiety, depression, and overall psychological distress) according to HADS guidelines [37, 38]. Higher scores indicate more psychological distress [37, 38]. The HADS has evidence of reliability and validity in early stage breast cancer patients [36, 39].

##### EuroQol 5-Dimension 5-Level questionnaire (EQ-5D-5L)

This instrument, assessing health status, consists of five items and a visual analogue scale [40]. The items cover five dimensions (mobility, self-care, usual activities, pain/discomfort, and anxiety/depression). Each dimension has five response levels from ‘no problems’ to ‘extreme problems.’ The visual analogue scale records the patient’s self-rated health from 0 to 100, with the highest score indicating ‘The best health you can imagine’ and the lowest score indicating ‘The worst health you can imagine.’ Responses to each item combine to form a five-digit number that describes the patient’s health state. A corresponding index value will be assigned according to a recent valuation study conducted in England [41]. The EQ-5D-5L has a large base of evidence and for validity and reliability in breast cancer patients and can also be used to conduct economic analyses [42].

##### Health care utilization

Health care utilization will be assessed using data routinely collected in Discover. The Discover-linked dataset includes coded information on health and social care resource utilization of individuals registered with a GP practice in the North West London region. Information is collected about the number and type of appointments from primary, secondary, and social care for each patient between diagnosis and 1-year follow-up.

##### Health care costs

The Discover-linked dataset also provides the current costs of health and social care to Clinical Commissioners in North West London based upon Commissioner local pricing. Information on the cost of each type of appointment is calculated routinely and collated together across health care settings to provide a measure of health and social care utilization of each patient.

##### OWise uptake

With patient informed consent, we will evaluate OWise uptake by reviewing timestamps that indicate logging in or modification of a specific function. This information will allow us to evaluate whether participants use the tool, which function patients use, and how long the tool is used for.

#### Contamination

Patient responses to items at each measurement time point will indicate contamination. A set of 19 items will ask participants to identify the use of supportive care services including self-management mobile phone applications or websites. If a participant says yes, we will ask them to name the source in a free-text box to determine whether or not OWise has been used. Prior to recruitment close, the statistician will assess the level of contamination and increase the sample size commensurately [43].

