### Control group

Participants in the control group will receive all standard information including leaflets and links to resources that patients usually receive at the time of a new breast cancer diagnosis. Participants in the control group will not be given information about the tool but will also not be explicitly prohibited from using the tool.

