#### OWise engagement

Participants will be provided with a unique invitation code linked to their study identification number to input when creating an OWise account. Timestamp data will be identified by the invitation code and extracted at the end of the study. The data will be linked to other study data by the unique invitation code.

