This study design may be limited by relying on patient-reports of OWise use to measure contamination. However, this is unavoidable due to data protection arrangements of the tool. Participants may also use similar mHealth tools, which could confound the results. The open-ended items assessing contamination will measure the use of other tools and enable us to control for these effects in analysis as much as possible. This study will also be limited by updates of the application. Post hoc analysis of differences before and after the updates will allow us to assess whether changes in the application reduce or enlarge any effects or change participant uptake.

This study will allow us to assess whether OWise, a patient-focused mHealth technology, can have an impact on self-management processes, HRQoL, and NHS health resource utilization. With the comparative nature of the study and conduct in the NHS system, this will have broad implications for the adoption of this tool by the NHS in future. If successful, this application can be modified to meet the needs of other tumor groups. This study is also applying new methods in a growing field of mHealth evaluation and can serve as an example for researchers in future.

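### Control-arm OWise use is detected only by a yes answer and a free-text name, so users may be missed and the per-protocol analysis may look falsely reassuring; a closed question at 12 months would help

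*Protocol article*

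**What the plan says.** All references are to the protocol article.

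- **Control group:** controls "will not be given information about the tool but will also not be explicitly prohibited from using the tool". The Background says that the app is free and listed in the NHS Apps Library.
- **Contamination:** "A set of 19 items will ask participants to identify the use of supportive care services including self-management mobile phone applications or websites". These items are put at every measurement time point. After a yes, "we will ask them to name the source in a free-text box to determine whether or not OWise has been used". The Discussion describes the same items with free-text boxes.
- **Sensitivity analysis:** controls who report OWise use are dropped. If the result then differs from the primary analysis, the primary result is declared not robust.
- **Discussion:** "This study design may be limited by relying on patient-reports of OWise use to measure contamination. However, this is unavoidable", the reason given being the data protection arrangements of the tool.
- **OWise uptake and OWise engagement:** with consent, "we will evaluate OWise uptake by reviewing timestamps that indicate logging in or modification of a specific function". "Participants will be provided with a unique invitation code linked to their study identification number to input when creating an OWise account", and "Timestamp data will be identified by the invitation code and extracted at the end of the study". The Analysis section uses these data only to describe uptake.

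The article plans no comparison of the free-text item with the timestamps, and no direct question about OWise at any time point.

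**The concern.** The detection route has two steps, and a user can be lost at either. She may not think of the app as a supportive-care service and answer no, or she may answer yes and not recall the name. In both cases she is classed as unexposed.

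The count also decides who leaves the per-protocol control group. A missed user remains in that group and moves its result toward the intention-to-treat result. The stated rule says only that dissimilar results undermine the primary finding, so similar results will naturally be read as support. Similarity has two possible causes, little contamination or poor detection, and the planned data cannot tell them apart. This matters because the article presents measuring and assessing contamination as a methodological contribution.

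**Working it through.** **The plan's own figure.** From the Sample size section: difference 5.90, SD 10.0, two-sided alpha 0.05, power 80%. The exact t calculation gives power 0.799 at 46 per arm and 0.808 at 47, so the stated 47 reproduces. 47/(1 − 0.23) = 61.04, stated as 61. No stated figure is in dispute.

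**Assumptions (not in the documents).** Let c be the true share of controls using OWise and s the share of those users that the item detects. Suppose that each user gets the full 5.9-point effect, nobody reports use falsely, and excluded controls are otherwise like the rest.

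**Formulas.**
- Intention-to-treat difference: 5.9 × (1 − c).
- Share of users left in the per-protocol control group: r = c(1 − s)/(1 − cs).
- Per-protocol difference: 5.9 × (1 − r).
- Gap between the two, as a fraction of the gap under full detection: s(1 − c)/(1 − cs).

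**Results.** Users are counted among 47 evaluable controls.

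| c | Users | Missed at s = 0.5 | ITT difference | Per-protocol, s = 1 | s = 0.8 | s = 0.5 |
|---|---|---|---|---|---|---|
| 5% | 2.4 | 1.2 | 5.61 | 5.90 | 5.84 | 5.75 |
| 10% | 4.7 | 2.4 | 5.31 | 5.90 | 5.77 | 5.59 |
| 20% | 9.4 | 4.7 | 4.72 | 5.90 | 5.62 | 5.24 |

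Worked line: c = 20% and s = 0.5 give r = 0.10/0.90 = 11%, and 5.9 × 0.889 = 5.24. The gap is 5.24 − 4.72 = 0.52, against 5.90 − 4.72 = 1.18 under full detection, a fraction of 0.40/0.90 = 0.44. At c = 5% the fraction is 0.475/0.975 = 0.49, that is 0.14 points instead of 0.30. With s = 0.8 the fraction is 0.76 to 0.79 over the same range of c. With s = 0 the two analyses coincide.

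**Scale.** The standard error of the planned comparison is 10 × √(2/47) = 2.06 points. Every gap above is smaller than that, so agreement between the two analyses is weak evidence even with perfect detection.

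**Timing.** The Analysis section defers analysis until all patients have completed the 1-year follow-up, so a 12-month answer can still define the per-protocol set. The sample-size increase is decided before recruitment closes, and timestamps are extracted only at study end. Neither a 12-month question nor a timestamp comparison can inform that increase.

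**The case against.** The strongest case on the other side is that this is a disclosed limitation with little effect. The Discussion says that OWise use in the UK is low, the tool's name is withheld from controls, and the items are repeated, so a use missed once may be caught later. The primary analysis is by intention to treat and never uses the count. Brief or occasional use would also dilute less than the full effect assumed above. All of this stands, and it limits the point to the sensitivity analysis. It does not remove the point, because the Discussion also says that no similar study has reported a contamination level.

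A reader might infer more, in four ways that the documents do not support.

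- **That contamination will be under-counted.** This is the plausible direction, but no sensitivity figure is given and the wording of the 19 items is not reproduced.
- **That the timestamps disprove the word unavoidable.** They are identified through a study-issued invitation code, which a control who downloads the public app would not have. Control-arm exposure remains self-reported.
- **That the sample-size increase will fall short and could be repaired.** With assumed c = 20% and s = 0.5, apparent use is 10%. The plan would set 47/0.9² = 58.02, so 59 evaluable per arm, where 47/0.8² = 73.4, so 74, are needed; power would be about 72%. Both inputs are assumptions, and the available checks arrive after the decision.
- **That reported control use can be divided by the intervention arm's naming rate.** Those participants were given the name and instructions, so the rate may not transfer. It is also imprecise: an observed 28 of 47 has an exact 95% interval of about 0.44 to 0.74, and 12 of 20 about 0.36 to 0.81.

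**Conclusion.** The point holds as a cheap improvement to the sensitivity analysis. The documents show that detection in controls depends on a yes answer followed by a recalled name, and that this alone defines the per-protocol exclusions. Users may be missed, and each one missed makes the two analyses look more alike. Under the stated assumptions, at 5% to 20% true use, half detection leaves about one to five users in a control group of 47. It cuts the expected gap between the analyses to 44–49% of its full size, a loss of about 0.15 to 0.66 points. At the low use that the article expects, this is minor. The article contains no contradiction here, and its statement about reliance on self-report is correct for controls.

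**What to change.** 1. At the end of the 12-month questionnaire, once all PROMs are submitted, ask control participants one closed question: whether they used OWise and, if so, when they first used it. Naming the tool then cannot affect any of that participant's PROMs.
2. Run the per-protocol analysis with exclusions based on either source, the free-text item or the closed question. Show separately the controls whose use began before the 3-month assessment, since only that use can dilute the primary endpoint.
3. As description only, report how often intervention participants with login timestamps name OWise in the free-text item. State that this is probably an optimistic guide to the item's sensitivity in controls, and do not use it as a divisor.
4. Add to the Discussion that possible under-reporting will be examined in this way, and that neither step can inform the sample-size increase.

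The cost is one extra question and some analysis wording, with no added visits or patients. The downsides are recall error at 12 months, particularly on when use began, and no answer from controls lost before then, for whom the free-text item remains the only source.
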